## Abstract

**Background:**

Stress is suggested to be an important factor contributing to the development and persistence of musculoskeletal pain. Although stress and pain interactions are well known, it remains largely unclear how (dys)function of the major stress systems (i.e., the autonomic nervous system and the hypothalamic-pituitary-adrenal axis) contributes to pain extent and duration, and what the underlying mechanisms are. A comprehensive characterization of the stress systems and their interactions with pain is needed to better understand how stress confers vulnerability for persistent pain.

**Aims:**

The primary aim of this study is to characterize stress system (dys)functioning (i.e., including basal levels, reactivity and recovery to acute stress, and chronic stress levels) in musculoskeletal pain groups with varying pain duration and extent, and to investigate the interaction between stress and pain at the psychosocial, (psycho)physiological and neural level. The secondary aim is to define the contribution of stress to pain trajectories, including chronification and recovery.

**Methods:**

A study with a cross-sectional and a longitudinal arm will be conducted in musculoskeletal pain groups with varying pain characteristics, including chronic widespread pain (fibromyalgia), chronic and subacute localized pain (low back pain), and pain-free controls (n = 35/group). To characterize pain trajectories (recovery/persisting), localized pain groups will be reassessed after six months. Stress and pain characteristics and functionality will be assessed using questionnaires, autonomic measures (alpha-amylase, blood pressure, heart rate, respiratory rate, skin conductance and skin temperature), hormonal concentrations (cortisol and oxytocin), quantitative sensory testing (pain thresholds, pain tolerances, conditioned pain modulation and temporal summation of pain), and magnetic resonance imaging (brain structure and function).

**Discussion:**

This study will provide crucial insights in the role of stress in the extent of pain symptomatology and in conferring risk for pain chronicity. Additionally, it will shed light on the underlying mechanisms of stress and pain interactions.

Trial registration: ClinicalTrials.gov (NCT06892977)

## 1. Introduction

Stress and pain are intricately and dynamically connected at various levels, both in acute and chronic contexts. Acute stress can influence pain perception, either amplifying or reducing sensitivity to painful stimuli in individuals with and without clinical pain [1–5], and can magnify self-perceived pain in individuals with chronic pain [6]. Conversely, pain can function as a stressor by triggering activation of the major stress response systems, i.e., the autonomic nervous system (ANS) and the hypothalamic-pituitary-adrenal (HPA) axis. The sympathetic branch of the ANS, also called the sympatho-adreno-medullary (SAM) system, increases the release of catecholamines (e.g., noradrenaline) in response to a stressor, leading to physiological changes including elevations in heart rate and blood pressure. This sympathetic activation suppresses parasympathetic activity, which in turn elicits bodily changes such as an increase in heart rate and a reduction in heart rate variability. Besides these changes in electrophysiological parameters, stress can swiftly elevate enzyme concentrations in saliva such as alpha-amylase (sAA) [7]. The SAM system is characterized by its rapid activation and quick recovery during and following a stressor. In contrast, the HPA axis has a delayed but longer lasting response through the release of cortisol, a well-known stress hormone that influences energy metabolism, cardiovascular function and the immune system [8,9]. Following a stressor, HPA axis activity is regulated by a negative feedback system that is at least in part mediated by limbic and frontal brain structures (e.g., amygdala, hippocampus, medial prefrontal cortex), to promote recovery and restore homeostasis [10]. Cortisol plays an important part in this recovery, although there are also other hormones involved in regulating the HPA axis’ activity, including oxytocin, a neuropeptide traditionally associated with social bonding and childbirth [11]. Given that our body’s response to stress is orchestrated within multiple systems and time scales, a comprehensive assessment of stress is warranted to gain a full picture of its interactions with pain.

While both acute stress and acute pain are designed to promote survival, persistence of either stress or pain is maladaptive and negatively affects well-being. Research has shown support for both elevated stress levels and dysregulation of the stress systems in people with persistent pain [12]. People suffering from chronic musculoskeletal (MSK) pain generally report higher levels of emotional distress compared to pain-free individuals [13]. Additionally, alterations in ANS functioning have been observed in chronic MSK pain conditions, as indicated by increased sympathetic and decreased parasympathetic modulation [14], blunted ANS reactivity (e.g., during a cognitive stressor) [15,16], and diminished or delayed parasympathetic reactivation during recovery from an acute stressor [15]. When stress is sustained over time, the HPA axis can become dysregulated, manifesting as either overactivity or underactivity of the system [17] . Signs of HPA axis dysregulation are observed in chronic MSK pain too, as both heightened and reduced basal cortisol levels, as well as increased and diminished cortisol reactivity [12] have been observed. These inconsistent findings might be explained not only by limited assessments of stress, but also by variations in duration and extent of the pain symptoms. Since pain is a potent stressor, individuals suffering from MSK pain may initially experience higher cortisol levels, which may lead to a rapid depletion of cortisol in response to repeated or persistent stress, potentially resulting in reduced cortisol levels as pain duration increases. This hypothesis is supported by observations in people with fibromyalgia, a widespread MSK pain condition, in which patients with a shorter disease duration showed increased hair cortisol levels, as a marker of chronic stress, while those with long disease duration show lower levels of hair cortisol (indicating a depletion of cortisol levels) [18]. This shows the importance of not only measuring hormones over a short (acute) period of time using saliva, serum, or urine samples, but to also include markers of longer (chronic) periods of cortisol exposure (e.g., cortisol concentrations from hair samples [19]). Yet, whether and how the multiple stress systems contribute to differences in pain extent and duration, and whether teasing those apart may explain some of the reported inconsistencies, remains to be tested.

A recent systematic review and meta-analyses from our group has shown evidence for the association of pain sensitivity with baroreceptor dysregulation and HPA axis dysfunction [20]. Findings showed that when acute stress is induced, an association between autonomic dysfunction and higher pain sensitivity can be observed in patients with chronic pain. However, the review also illustrates that studies investigating the association between HPA axis functioning and experimental pain are limited. More research investigating the interactions between both the ANS and the HPA axis with static and dynamic experimental pain paradigms, and exploring the reactivity and recovery of these stress systems with standardized, effective stressors is necessary to pinpoint underlying mechanisms of the pain-stress interactions [20]. On a neural level, research has shown that when pain becomes chronic, brain activity involved in sensory processing shifts towards brain networks engaged in emotional processing (i.e., the corticolimbic system [21]. Interestingly, these networks overlap with areas involved in stress response regulation [21], suggesting shared mechanisms. A study reported that individuals with chronic MSK pain as well as pain-free controls with stronger cortisol responses to an acute painful stressor showed reduced pain-related activation in the insula and somatosensory cortex [22], thus illustrating the stress-pain interaction on a neural level too. While there is clear evidence linking pain with stress at multiple levels, how stress system dysfunction contributes to increased risk for pain persistence, and what the underlying (psycho)physiological and neural mechanisms are largely unclear.

To shed light on the underlying mechanisms of pain and stress interactions and their contribution to pain extent and chronification, the aim of the current STRAIN (‘stress in pain’) study is to characterize stress system functioning and its relation to pain in individuals with subacute versus chronic, and localized versus widespread MSK pain, to allow comparison of groups with different pain characteristics in terms of pain extent and duration. A comprehensive mapping of both ANS and HPA axis stress systems will be used to assess basal levels, reactivity and recovery of acute stress, and chronic stress exposure. Interactions between stress and psychosocial, (psycho)physiological, and neural correlates of pain will be investigated. Additionally, the secondary aim of this study is to characterize stress system responses over time and their role in MSK pain recovery and chronification. Therefore, stress system functioning and its interactions with pain will be reexamined after six months in the patients with subacute MSK pain.

## 2. Materials and methods

### 2.1. Study design

The STRAIN study protocol was pre-registered at ClinicalTrials.gov (NCT06892977) and reported in accordance with the Strengthening the Reporting of Observational Studies in Epidemiology (STROBE) statement [23]. Recruitment for this study commenced on 8 February 2025 and is anticipated to conclude by 1 June 2026. Study completion and the release of initial results are expected by 1 December 2026. The study consists of a cross-sectional arm and a longitudinal arm (i.e., follow up at six months). A total of 140 participants will be recruited for this study, across four groups (n = 35/group): (1) a group with chronic widespread MSK pain (i.e., fibromyalgia), (2) a group with chronic localized MSK pain (i.e., non-specific low back pain (LBP) for ≥six months), (3) a group with subacute localized MSK pain (i.e., non-specific LBP for <three months), and (4) a pain-free control group (no history of chronic pain or current pain). All groups will participate in the cross-sectional arm which consists of a four-hour lab assessment at Ghent University (Ghent, Belgium) and three (consecutive) days of home assessments. Participants of the localized MSK pain groups will also participate in the longitudinal arm consisting of the same assessments, supplemented with assessing pain persistence or recovery. The study will be performed in accordance with the Code of Ethics of the World Medical Association (Declaration of Helsinki) and the international ethical and scientific quality standards accepted by the International Conference on Harmonization guidelines for Good Clinical Practice. Several patient-groups were involved in various stages of developing the study protocol, providing insights into the research and helping to minimize participant burden. The study protocol and data management plan were approved by the Medical Ethics Committee of Ghent University/Ghent University Hospital and all participants will provide written informed consent prior to study participation.

### 2.2. Participants

Participants will be recruited through an existing database of volunteers for pain research, advertisements (e.g., social media, newsletters), and the distribution of flyers at private practices, (university) hospitals and public places.

All participants must be Dutch speaking, aged between 18 and 45 years, and have a body mass index between 18.5 kg/m^2^ and 35 kg/m^2^. Inclusion criteria for patients in the MSK pain groups are an average pain intensity of ≥2/10 on a visual analogue scale (VAS) and a pain-related disability of ≥14/70 on the Pain Disability Index (PDI) [24]. Participants of the chronic widespread MSK pain group will require proof of a primary fibromyalgia with chronic widespread pain diagnosis. As different diagnostic criteria have been used over time, researchers will check whether participants comply with the 2010 ACR-criteria [25]. To ensure that pain complaints are of MSK nature, only individuals with non-specific (primary) LBP will be included, with those suffering from LBP less than three months being eligible to participate in the subacute localized MSK pain group and those with LBP equal or more than six months being eligible to participate in the chronic localized MSK pain group. Pain-free controls should not report current pain, a history of chronic pain, or treatment for a pain condition in the last six months.

Anyone using hormonal replacement therapy, drugs ≥ 1x/week, having no stable use of medication (if applicable) one month before the study visit, a contra-indication for magnetic resonance imaging (MRI; i.e., electrical or mechanical implants, electrodes, or metal fragments in the body, being claustrophobic, weighing >150 kg), or being menopausal, pregnant, less than one year postnatal or lactating will be excluded. Furthermore, having a (history of a) psychiatric, cardiovascular, endocrine, or neurological condition (e.g., diabetes, epilepsy), spinal traumata, spinal surgery, or a severe communicative disorder or cognitive disability will not be eligible. The Dutch version of the simplified version of the Mini International Neuropsychiatric Interview (MINI) [26] based on the Diagnostic and Statistical Manual of Mental Disorders, Fifth edition (DSM-V) will be consulted in case of the presence of potential psychiatric conditions. People with LBP will be excluded if they suffer from specific LBP (i.e., LBP due to a clear identifiable pathology, e.g., lumbar radiculopathy).

Demographical characteristics and potential confounders will be assessed, including age, biological sex assigned at birth and gendered pain dynamics, height and weight (body mass index), ethnicity, hormonal cycle and contraceptives, medication use, drugs use, alcohol use, nicotine use, educational level, occupation, comorbidities, sleep experience (quality and quantity), and used pain management strategies. These will also be used to examine whether participants complied with the instructions described below.

### 2.3. Setting

Eligibility will be assessed through an online screening questionnaire and potential participants will be contacted for additional information, if required. Eligible participants will receive a secure link to health-related questionnaires ten days prior to the study. Research Electronic Data Capture (REDCap) software [27,28], a secure web-based software platform designed to facilitate data collection and management for research, will be used to collect self-reported data online.

Participants will be asked to adhere with following instructions in preparation for the lab assessments (if applicable and medically permissible): be awake for ≥two hours, refrain from consuming nicotine, other beverages than (still) water, and food two hours prior to the study visit [4], strenuous mental or physical activity <24 hours prior to the study visit [29], opioid use < 24 hours prior to the study visit [30], postpone the intake of medication with analgetic effects or affecting blood pressure until after the study visit [31,32], and maintain a normal sleeping routine before and three days after the study visit. A normal sleep routine is defined as going to bed and waking up at the time that is most common in the participant’s daily routine.

The lab assessment consists of (1) assessments of stress (using self-reported and physiological measures), (2) assessments of pain (using self-reports, quantitative sensory testing (QST)), (3) assessments of the brain (using (functional)MRI). After the study visit, participants will be instructed to collect saliva samples at home for three days as part of the physiological stress assessments. After a follow-up period of six months, the same assessments will be repeated. In addition, pain persistence and recovery will be assessed using a questionnaire. An overview of the procedures, measures and study design is depicted in Fig 1. For an overview of all measures and their timing, see Table S1.

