Non-induced stress system functioning will be assessed at home. Participants will collect saliva samples for three (consecutive) days. Samples at home will be acquired directly after awakening (timepoint at home one or h1), 30 minutes after awakening (h2), 45 minutes after awakening (h3), at 16.00h (h4) and at 21.00h (h5). This will allow characterization of the first sample (h1), the cortisol awakening response (CAR) (mean increase = (h2 + h3/ 2*h1)), and basal cortisol levels throughout the day (Area Under the Curve (AUC) h1-h5) [52]. Self-collection has been previously used in chronic MSK pain [53]. Adherence to the instructions will be assessed, and the timing of sampling will be verified through documentation of the timepoint (by taking a picture of the sample with a timestamp) at which each sample is collected.

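### Home cortisol samples h4 and h5 are fixed to clock time while wake time is left free, so AUC h1-h5 is not comparable for night workers and other daytime sleepers

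*Protocol article*

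**What the plan says.** - **Sleep instruction (protocol article, 2.3 Setting).** Participants are to "maintain a normal sleeping routine before and three days after the study visit". The definition follows: "A normal sleep routine is defined as going to bed and waking up at the time that is most common" for that person. No clock window is attached.
- **Eligibility (2.2 Participants).** People must be "aged between 18 and 45 years". The published exclusions cover, among others, "Anyone using hormonal replacement therapy, drugs ≥ 1x/week, having no stable use of medication (if applicable) one month before the study visit", MRI contra-indications, reproductive status, and "having a (history of a) psychiatric, cardiovascular, endocrine, or neurological condition (e.g., diabetes, epilepsy), spinal traumata, spinal surgery". Neither shift work nor sleep schedule is listed.
- **Home sampling (2.6).** On each of three days, saliva is taken "directly after awakening (timepoint at home one or h1), 30 minutes after awakening (h2), 45 minutes after awakening (h3"), and then "at 16.00h (h4) and at 21.00h (h5"). The first sample, the awakening response (from h1-h3) and the AUC over h1-h5 are the derived measures. Each sampling time is documented by a time-stamped picture.
- **Covariates (2.2).** Occupation and sleep quality and quantity are recorded as potential confounders. These data also serve to check compliance with the instructions.

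**The concern.** The schedule uses two time scales. Three samples follow the participant's own waking and two follow the wall clock. Joining them in one AUC gives the same part of the waking day for everyone only if everyone wakes at roughly the same hour, and the sleep instruction does not require that. A night worker who habitually sleeps by day meets the definition exactly, so a compliance check would not flag that person. For a rotating-shift worker the definition may point to no single wake time at all.

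Basal stress-system level is part of the primary aim. Section 2.11 predicts lower basal cortisol in fibromyalgia and higher cortisol in chronic low back pain than in controls. If daytime sleeping were more common in one group, part of a difference in AUC, h4 or h5 would reflect when people woke rather than how their HPA axis works. The localized pain groups repeat the assessments at six months, so a change of work pattern between the two periods could likewise look like a change in cortisol.

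**Working it through.** The plan gives no figure of its own for this point, and its sample-size calculation is not affected. The check is clock arithmetic on the stated schedule.

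**Inputs (section 2.6).** With wake time w: h1 = w, h2 = w + 0:30, h3 = w + 0:45, h4 = 16:00, h5 = 21:00. Section 2.3 leaves w free.

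**Formulas.** Time from waking to h4 = 16:00 - w. Time from waking to h5, which is also the AUC span while h1 is the first sample, = 21:00 - w.

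| Wake time | h4 after waking | h5 after waking = AUC span | Span relative to 07:00 |
|---|---|---|---|
| 07:00 | 9 h | 14 h | 100% |
| 10:00 | 6 h | 11 h | 79% |
| 12:00 | 4 h | 9 h | 64% |
| 14:00 | 2 h | 7 h | 50% |
| 15:00 | 1 h | 6 h | 43% |
| 16:00 | 0 h | 5 h | 36% |

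**Order of samples.** h3 reaches h4 when w + 0:45 = 16:00, that is w = 15:15. For any earlier waking the order h1 to h5 is intact. Between 15:15 and 16:00, h4 falls among the waking samples. After 16:00 it precedes h1.

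**Does dividing by time repair it?** Take one identical cortisol curve for everybody, driven only by s, the hours since waking. The curve is an assumption for illustration, in arbitrary units, and is not from the documents:

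- s < 1: c(s) = 10 + 5·exp(-((s - 0.55)/0.35)²)
- s ≥ 1: c(s) = 2 + 9·exp(-(s - 1)/4)

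The waking samples are the same for every w: c(0) = 10.42, c(0.5) = 14.90, c(0.75) = 13.61. Their trapezoids add 6.33 + 3.56 = 9.89.

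- Waking 07:00: h4 = c(9) = 3.22 and h5 = c(14) = 2.35. AUC = 9.89 + 8.25 × (13.61 + 3.22)/2 + 5 × (3.22 + 2.35)/2 = 93.2. Per hour: 93.2/14 = 6.7.
- Waking 14:00: h4 = c(2) = 9.01 and h5 = c(7) = 4.01. AUC = 9.89 + 1.25 × (13.61 + 9.01)/2 + 5 × (9.01 + 4.01)/2 = 56.6. Per hour: 56.6/7 = 8.1.

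With the same physiology, the AUC falls by 1 - 56.6/93.2 = 39%, h4 rises from 3.2 to 9.0, and AUC per hour rises from 6.7 to 8.1. Total AUC and time-scaled AUC are thus wrong in opposite directions, so scaling by span is not a repair. Sample order is intact in this example.

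**What is untouched.** h1 and the awakening response use wake-anchored samples only. No value of w lets the clock-timed samples displace them.

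**The case against.** The strongest reply has four parts.

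1. **The article condenses a fuller protocol.** A shift-work question may sit in the screening questionnaire, so eligibility of night workers is inferred from silence. That stands as a caution. The conflict between a free wake time and clock-fixed samples does not rest on silence: both rules are stated.
2. **The study already holds the data to find these people.** Occupation and sleep quality and quantity are recorded, and the h1 pictures give an approximate wake time on each home day. It would be wrong to say that the plan collects nothing useful. But a time stamp only shows that h4 came 2 h after waking; it cannot supply the later waking hours that were never sampled.
3. **A reader might infer that sample order and the whole daily profile are invalid for all night and rotating-shift workers, awakening response included.** The documents do not support that. Order holds for any waking before 15:15, a rotating worker on day shifts is unaffected, and the awakening response does not use h4 or h5.
4. **A reader might put a figure on the bias.** If one group had 10 percentage points more daytime sleepers and AUC were proportional to span, its mean AUC would shift by 0.10 × (1 - 9/14) = 3.6% for waking at 12:00, 0.10 × (1 - 7/14) = 5.0% at 14:00, or 0.10 × (1 - 5/14) = 6.4% at 16:00. Every input except the span is assumed, and proportionality already fails on the curve above (span down 50%, AUC down 39%). These figures are not estimates for this study.

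**Conclusion.** The concern holds in a limited form. As published, a daytime sleeper can comply fully and still give h4, h5 and AUC h1-h5 values that do not describe the same part of the waking day as those of a day-schedule participant. The AUC span is half as long for waking at 14:00 and 36% as long for waking at 16:00, relative to 07:00. These spans follow from the stated schedule alone. The 39% fall in AUC depends on an illustrative curve that follows time since waking.

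Neither the size nor the direction of any bias between groups can be computed, because the documents give no shift-work prevalence, overall or by group. These outcomes are best called not comparable unless handled, rather than invalid. The affected measures are h4, h5 and AUC h1-h5. The first sample, the awakening response, hair cortisol and all laboratory and MRI outcomes fall outside this point.

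**What to change.** - Add one screening question on night or rotating-shift work around the visit. Ask it retrospectively of people already enrolled, and again before the six-month home sampling.
- Use the h1 time stamps to identify daytime sleepers, with the wake-time cut-off written down before cortisol results are seen. The documents give no cut-off; the table above shows what each choice would admit.
- Leave the h4, h5 and AUC h1-h5 of these participants out of the main basal-cortisol comparison, and report a sensitivity analysis that includes them.
- Compute the AUC from recorded rather than nominal sampling times for everyone else.
- Report the number of affected participants by group, so that readers can judge any imbalance.

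Keep these participants in all other outcomes. Excluding shift workers from the whole study would also discard their stress-test, sensory-testing, MRI and hair data, and would select on employment, possibly to a different degree in each group. The cost is one question, a few sentences in the analysis plan and a small loss of home-sample data. The sample size does not change.
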